### Anthropometric and body composition

Weight, height and waist circumference at the lower value were measured using standardized procedures [19] and body composition estimated by bioelectrical impedance, using the leg-to-leg Tanita scale (BC-558). Height was measured using a portable stadiometer. Overweight and obesity classification of the World Health Organization was used [20].

### Statistical analysis

Intent to treat analysis will be conducted through mixed models longitudinal analysis taking into account the cluster effect (classes) [21]. These mixed models allow for the exploration of factors associated with BMI variation and the other outcomes in a multilevel analysis where the class was on the second level and the individual measures on the first level. Data analysis will be performed using the Statistical Analysis System, version 9.3 (SAS Institute Inc, Cary, NC).

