## Methods

### Study design

The trial is a randomized community controlled trial labeled PAAPPAS, which stands for “parents, students, *community health agents* and teachers for healthy eating”. The intervention aimed at reducing excessive weight gain among adolescents combining primary prevention at schools with the primary care health system, through the FHS Program.

Intervention will occur during the school year of 2016 and target fifth and sixth graders from 18 public schools (9 interventions and 9 controls) in the municipality of Duque de Caxias, metropolitan area of Rio de Janeiro, Brazil.

Primary intervention in the school by trained teachers will provide the overall basis for a healthy lifestyle, including food intake, physical activity and sedentary habits. For adolescents diagnosed with excessive weight, household activities will provide additional motivation to change these behaviors. Trained community health agents (CHA) from the FHS Program will visit the families of adolescents with overweight or obesity every month, integrating activities with adolescent and his/her family.

The study will be conducted according to the Consolidated Standards of Reporting Trials (CONSORT) guidelines for cluster-randomized trials [12]. The Ethics Committee of the Institute of Social Medicine (State University of Rio de Janeiro, Brazil) approved the protocol. Written informed consent was obtained from all the participants’ parents.

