### Sample size calculation

The sample size for the secondary prevention intervention was estimated based on a standard deviation of body mass index (BMI) equals 3.0; the difference from baseline to the end of intervention among those with overweight and obesity of 1.1 BMI units and the intracluster correlation coefficient was 0.02, according to a previous study conducted in schools [7]. Considering 80 % power and a 5 % significance level, 117 are needed per group to compare intervention with control. In order to reach this sample assuming a prevalence of overweight/obesity of 20 %, the total sample size needed at school is of 2340 participants. Given an intracluster correlation of 0.02, a 2500 sample size was the goal.

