**Fig. 1 Fig1:**
[figure not shown]
Study design

Schools were randomized half in the control group and half in the intervention group based on number of students using opaque envelopes, in the presence of investigators not involved in the current study. Schools will remain in their allocated group for the duration of the study. Participants in the control arm will receive only the routine activities for healthy behaviour of the school.

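### Schools were randomised but the mixed model clusters only on class, so standard errors are too small whenever outcomes vary between schools beyond class

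*Protocol article*

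**What the plan says.** The randomisation paragraph under Setting and participants states: "Schools were randomized half in the control group and half in the intervention group". Study design gives the number of units: "18 public schools (9 interventions and 9 controls".

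The Statistical analysis section names a different cluster. It plans "mixed models longitudinal analysis taking into account the cluster effect (classes" and then sets out the levels: "the class was on the second level and the individual measures on the first level". The same model is meant for BMI and for the other outcomes. The article mentions no school random effect, no variance estimate robust to school clustering and no degrees of freedom based on schools.

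The Sample size calculation section takes one ICC from earlier work: "the intracluster correlation coefficient was 0.02, according to a previous study conducted in schools". It does not say whether that value refers to schools or to classes. Study design also commits the trial to the CONSORT guidance for cluster-randomised trials.

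**The concern.** In a cluster-randomised trial the information on the arm effect comes from variation between the randomised units. Here there are 18, which leaves 18 − 2 = 16 degrees of freedom. Classes in the same school have the same allocation, school environment and intervention programme. A model with class as its only cluster treats them as independent replicates of the allocation. With 3 to 6 classes per school (assumed), that is 54 to 108 units in place of 18.

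If schools differ in the outcome beyond what class captures, that variation enters the true error of the arm difference but is largely averaged away in the model's estimate of it. Confidence intervals are then too narrow and false positives too frequent. Both BMI hypotheses listed under Outcomes (0.4 units for primary prevention, 1.1 for secondary prevention) and the secondary outcomes rest on this model. The Discussion ties a positive result to training all community health agents in the municipality, so a false positive would have practical consequences.

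**Working it through.** **The plan's own figure.** The inputs are "standard deviation of body mass index (BMI) equals 3.0", a difference "among those with overweight and obesity of 1.1 BMI units", 80% power and two-sided 5% (sidedness is not stated, but two-sided reproduces the figure):

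n = 2 × (1.96 + 0.8416)² × 3.0² / 1.1² = 116.8, so 117 per group.

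This matches the stated 117. It contains no clustering term, so it does not show which level the ICC belongs to.

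**Inputs for the check**
- From the article: 18 schools, 9 per arm; 2500 students, so 2500/18 = 138.9 per school; 20% overweight/obese, so 500/18 = 27.8 per school; ICC 0.02.
- Assumed: c = 3 to 6 classes per school; equal sizes; one analysed value per student; the ICC applies to that value; the ICC is split between a school part s and a class part k, with s + k = 0.02.

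**Formulas** (total variance 1, M students per school, m = M/c per class, K = 9c classes per arm)
- True variance of an arm mean: V = [s + k/c + (1 − s − k)/M] / 9
- Variance that a class-only model estimates: W = [k + (1 − s − k)/m + s(K − c)/(K − 1)] / K
- SE ratio R = √(V/W); true type I error = 2 × P(Z > 1.96/R)

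**Worked case: all students, c = 5, s = 0.02, k = 0**
- V = (0.02 + 0.98/138.9)/9 = 0.003006. The design effect is V × 9 × 138.9 = 3.76, which is also 1 + 137.9 × 0.02.
- W = (0.98/27.78 + 0.02 × 40/44)/45 = 0.001188, a design effect of 1.485.
- R = √(3.758/1.485) = 1.59; type I error = 2 × P(Z > 1.232) = 21.8%.

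**Same case, overweight/obese students**
- The design effects are 1.536 (true) and 1.081 (class-only).
- R = 1.19; type I error = 2 × P(Z > 1.644) = 10.0%.

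**Range over c = 3 to 6**

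| School part / class part of ICC | SE ratio, all | Type I error, all | SE ratio, overweight/obese | Type I error, overweight/obese |
|---|---|---|---|---|
| 0.02 / 0 | 1.43-1.64 | 17-23% | 1.16-1.20 | 9-10% |
| 0.01 / 0.01 | 1.23-1.35 | 11-15% | 1.08-1.11 | 7-8% |
| 0.005 / 0.015 | 1.12-1.19 | 8-10% | 1.04-1.05 | 6% |
| 0 / 0.02 | 1.00 | 5% | 1.00 | 5% |

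**Simulation** (20,000 runs per scenario; t-test on class means, which corresponds to a balanced class random-effect model). With 5 classes per school, in the row order of the table, rejection rates were 21.5%, 13.9%, 9.1% and 4.8% for all students, and 9.5%, 6.7%, 6.0% and 4.8% for overweight/obese students. A t-test on the 18 school means rejected in 4.7-5.2% of runs in every scenario, with 3 or 5 classes.

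**The case against.** The strongest reply is that nothing in the article shows school-level variance beyond class. Only one ICC is given, its level is unstated, and with no school part the class model holds its 5%. This stands, and it means the point must be conditional. A reader might infer that every standard error and p-value in the trial will be wrong; the documents do not support that. The mismatch itself remains: a school-randomised trial should not need zero school variance for its test to be valid.

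A second reply is that the figures describe a test on one value per student, whereas the plan is longitudinal. This also stands. In the longitudinal model the size depends on the ICC of BMI change, which the article does not give. The table is an illustration, not a forecast.

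Third, the trial was sized for overweight/obese students, for whom the inflation is modest, about 6-10% when school variance is present. That is correct; the larger figures belong to the all-student comparison.

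Fourth, an article condenses its analysis plan. That would excuse silence about the cluster level, but here a level is named twice and it is not the randomised one.

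A reader might also infer from the two-level description that the model has no student level, so that a student's baseline and follow-up values are treated as independent. The documents do not support this. The wording is condensed, the analysis is called longitudinal, and covariance details are commonly left to the full plan. That error would also enlarge the standard error of the change contrast, the opposite direction to the one described here.

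**Conclusion.** The point holds in conditional form. The article states an analysis cluster (class) that is not the randomised unit (school). Standard errors of the arm comparisons are too small, and p-values too low, whenever outcomes vary between schools beyond class.

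How far depends on two quantities that the article does not give: the school share of the ICC and the number of classes per school. Under the stated assumptions the true type I error of a nominal 5% test runs from 5% to about 23% for all students and from 5% to about 10% for overweight/obese students. The lower end applies only if schools add no variance of their own. Because the stated level is what is at fault, the text should be corrected before any arm comparison is run.

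**What to change.** In Statistical analysis, name school as the cluster. Fit repeated measures within students within schools, with class as an optional level between student and school. Include random school and school-by-time effects; the second is needed because a school intercept alone cancels from the change contrast. Test the arm effect with small-sample degrees of freedom based on the 18 schools, about 16, for example by Kenward-Roger.

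An acceptable alternative is ANCOVA of follow-up BMI on baseline BMI with a random school effect. It is not equivalent to the longitudinal model, because baseline adjustment and the handling of students without follow-up differ.

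Adjust for school size only if the randomisation was in fact stratified or matched on it. The article says "Schools were randomized half in the control group and half in the intervention group based on number of students using opaque envelopes" and describes no strata or pairs. If such terms are added, the degrees of freedom fall below 16.

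The change needs revised wording and a few lines of SAS code, and no new data. The price is wider confidence intervals.

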### Data collection at school

Anthropometric measures, food consumption and a questionnaire are being collected at baseline [March-April] and post-intervention [November-December] using personal digital assistant (PDA). Students will complete a structured questionnaire under the supervision of field researchers using PDA and the CHA will take anthropometric measurements.

Food consumption will be assessed by 24-h recall and a short (23 items) food frequency questionnaire (FFQ), which is a reduced version of an FFQ validated for adolescents of Rio de Janeiro [16]. The 24-h recall will use the BrasilNutri software, entering data during interviews in schools. The software encompasses a computerized food database developed for the 2008-2009 nationwide dietary survey [17].

Measurement of physical activity will include the evaluation of exercise, leisure activities, commuting to school, and sedentary activities (video games, television and computer time) measured by questionnaire [18] and in a subgroup by accelerometer (GT3X Actigraph).

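### The stated two-level model (measures within class) leaves out the student and the randomised school, so the standard error for BMI change would be wrong by an amount the protocol does not fix

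*Protocol article*

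**What the plan says.** The Statistical analysis section promises "mixed models longitudinal analysis taking into account the cluster effect (classes") and describes the structure as "in a multilevel analysis where the class was on the second level and the individual measures on the first level". Class is the only cluster named.

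Three other places bear on this:

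- **Data collection at school.** Anthropometry, food consumption and the questionnaire "are being collected at baseline [March-April] and post-intervention [November-December"], so each student contributes two BMI values.
- **Sample size calculation.** The planned effect is "the difference from baseline to the end of intervention among those with overweight and obesity of 1.1 BMI units", which is a change. The standard deviation of BMI is 3.0 and the intracluster correlation 0.02.
- **Setting and participants, text below Fig. 1.** "Schools were randomized half in the control group and half in the intervention group". Study design gives the number: "18 public schools (9 interventions and 9 controls").

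**The concern.** The data have the structure visit within student within class within school. The stated levels go from measures straight to class. If that model is fitted, two things go wrong with the arm-by-visit effect.

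- **Student level missing.** A student's stable BMI cancels from that student's change, but the model does not know this. It leaves between-student variance in the residual and uses it to judge the change. This makes the standard error too large. The class intercept does not help, because it cancels from a change as well.
- **School missing.** If BMI change varies between schools, nothing in the model carries that variation to the randomised comparison. This makes the standard error too small.

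The two errors pull in opposite directions. At stake are the width of the confidence interval for BMI change, the chance of detecting effects below the planned 1.1 units, and, under some values, the false-positive rate. Waist circumference and body fat are affected in the same way if they are analysed with the same structure.

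**Working it through.** **Reproducing the plan's figure.** With SD 3.0, difference 1.1, two-sided 5% and 80% power: n = 2 × (1.960 + 0.842)² × 3.0² / 1.1² = 116.8, so 117 per group. This matches the article. It uses the SD of a single BMI value and no clustering.

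**Inputs from the article.** σ = 3.0; ICC = 0.02; 18 schools; goal of 2500 students; 20% overweight or obese. Hence 2500 / 2 = 1250 students per arm and 2500 / 18 ≈ 139 per school. Among the overweight, 0.20 × 1250 = 250 per arm and about 28 per school.

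**Assumptions not in the article.** Within-student correlation ρ of BMI over the school year, shown for 0.75, 0.90 and 0.95; school ICC of BMI change, shown for 0 and for 0.02 (the article's ICC carried over to change).

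**Formulas.** The effect is a difference of two changes, built from four cell means of n students each.

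- Model as written: variance = 4σ²(1 − ICC)/n.
- True variance: 4σ²(1 − ρ)/n × DE, with DE = 1 + (m − 1) × ICC of change and m students per school.
- Ratio of standard errors = √[(1 − ICC) / ((1 − ρ) × DE)].

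For the overweight, DE = 1 + 27 × 0.02 = 1.54. For all students, DE = 1 + 138 × 0.02 = 3.76.

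**Ratio of stated to true standard error.**

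| Setting | ρ = 0.75 | ρ = 0.90 | ρ = 0.95 |
|---|---|---|---|
| No clustering of change (DE = 1) | 1.98 | 3.13 | 4.43 |
| Overweight, ICC of change 0.02 | 1.60 | 2.52 | 3.57 |
| All students, ICC of change 0.02 | 1.02 | 1.61 | 2.28 |

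For all students with clustered change the ratio equals 1 when 1 − ρ = 0.98 / 3.76 = 0.26, so at ρ ≈ 0.74. Below that the stated standard error is too small; at ρ = 0.50 the ratio is 0.72.

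**Simulation check** (18 schools, 5 classes of 28 each, class random intercept, 8 replicates per setting). The fitted two-level standard error was 0.167, 0.166 and 0.165 for the three values of ρ. The ratio to the true standard error was 1.98, 3.11 and 4.37 without clustering of change, and 1.01, 1.60 and 2.25 with a school ICC of 0.02 on change.

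**Consequence for the overweight comparison, n = 250 per arm.** Stated SE = √(36 × 0.98 / 250) = 0.376, so the 95% half-width is 1.96 × 0.376 = 0.74. This figure does not depend on ρ. With pairing respected and no clustering of change, SE = √(36 × (1 − ρ) / 250) = 0.190, 0.120 and 0.085, giving half-widths of 0.37, 0.24 and 0.17.

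The chance that a true effect δ is declared significant under the stated model is Φ[(δ − 0.736) / true SE]:

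- **δ = 1.1 (the plan's target).** No clustering of change: 97%, 99.9% and above 99.9%. With ICC 0.02 on change (true SE 0.236, 0.149, 0.105): 94%, 99% and above 99.9%.
- **δ = 0.55 (half the target, for illustration only).** No clustering of change: 16%, 6% and 1%, against 83%, 99.6% and above 99.9% with a student level.

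**Consequence for all students, n = 1250 per arm.** Stated SE = √(36 × 0.98 / 1250) = 0.168, half-width 0.33. For the 0.4-unit target in the Outcomes section, the same formula gives 80%, 91% and 97% without clustering of change. With ICC 0.02 on change (true SE 0.165, 0.104, 0.074) it gives 67%, 75% and 83%, against 68%, 97% and above 99.9% for a model that has both levels right. The actual type I error in that clustered case is 4.5% at ρ = 0.75.

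These are normal approximations; a test on 18 − 2 = 16 school degrees of freedom would shift the power figures somewhat but not the ratios.

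**The case against.** The strongest reply is that the missing student level is a literal reading of one sentence in a condensed article. Calling the model longitudinal suggests repeated measures on students. In SAS, which the article names, an unstructured within-student covariance can be fitted without adding a random-effect level, and an author could still describe class as the second level. The fuller plan may specify this. That stands as a reason for caution: the article does not prove that a wrong model will be run. It does not remove the point, because the article does not merely stay silent on structure. It assigns the levels, and the assignment omits the student.

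A second reply is that the first-level unit may be one change score per student. The section does mention BMI variation. On that reading there is a valid estimate of change and no inflation from lost pairing. So it would be wrong to say that the sentence fails on every reading. The article does not say that a change score is used, and the school would still be missing.

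A third reply is that the harm to the planned comparison is small. This largely stands. At 250 overweight students per arm, power for 1.1 units is about 95% or more over the assumed range. A calculation at 117 per group would look worse, but the article's goal of 2500 students implies about 250.

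**Conclusion.** The level description is wrong for a longitudinal analysis of students measured twice in randomised schools, and following it gives a wrong standard error for the arm-by-visit effect. For ρ of 0.75 to 0.95 the standard error is too large by a factor of about 2.0 to 4.4 if change does not cluster. With a school ICC of 0.02 on change, the factor is about 1.6 to 3.6 in overweight students and 1.0 to 2.3 in all students. Both ρ and the ICC of change are assumptions. The main cost is a wider interval and lost power for effects smaller than 1.1 units.

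A reader might infer more: that intervals are certainly several times too wide, or that the type I error is near zero throughout. The article does not support this. It gives no within-student correlation, and in the all-student analysis the omitted school variation can cancel the inflation (ratio about 1.0 at ρ = 0.75) or reverse it (below about 0.74). Nor does the point put the planned 1.1-unit comparison at serious risk. Moderate severity is right: correct it before analysis, but it does not invalidate the trial.

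**What to change.** Replace the level description in the Statistical analysis section with wording such as: BMI at the two visits (level 1) within student (level 2) within cluster (level 3); the intervention effect is the arm-by-visit term. Fit either a student random intercept or an unstructured 2 × 2 within-student covariance (in PROC MIXED, REPEATED visit with SUBJECT = student). Add a cluster-by-visit term at the randomised school, so that the cluster effect acts on the change and does not cancel. Class may stay as an additional level. Use the same structure for waist circumference and body fat.

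If a within-student covariance or a single change score per student was intended all along, say so in that sentence and name the school as the cluster.

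The cost is one sentence and a line or two of SAS code. No new data or students are needed.

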## Discussion

This is the first study that integrates school intervention with primary health care to prevent excessive weight gain among adolescents. Our previous studies and most of the literature have shown inconsistent results of studies based on only in the school, thus this is a promising study.

Our first school-based prevention trial was based on exchange sodas by water [7] and was inspired in a United Kingdom study that showed positive results with this approach [22]. In contrast with the British study, our results did not observe reduction in total intake of sugar; even though positive behavior changes were verified, adolescents increased the intake of sugary fruit-based drinks in replacement of sodas. The study coincided with the moment when food industry boosted the market of processed fruit-based drinks, which have as much or higher amount of sugar than sodas [7]. Therefore, in the second version of the study [10] we targeted the most important contributors of sugar intake in Brazil (all sugar sweetened beverages, sweets, cookies) [23] and behavior modifications were achieved, but without change in the weight gain.

In 2014, we tested a secondary prevention intervention of obesity in one school, mainly focusing on increasing physical activity of overweight/obese students and inviting their families to come to school to discuss possible strategies for changing lifestyle. However, family participation was minimal and overweight or obese adolescents did not enrolled in the after-school physical activity classes (unpublished results). The present study includes the positive results in changing behavior from previous ones and emphasis an interaction with primary health care based on family strategy.

We expect that FHS will facilitate family participation, which is very low in low-income communities. All families to be included in the study live in catchment areas of the FHS units allowing for this innovative approach combining primary and secondary prevention to address the escalating public health problem of obesity in Brazil.

The CHA act in the territory in which she/he is affiliated and serve as a mediator between families and health professionals. The family within the community is an active subject in the care process. This involves considering the family’s background and empowering families to face the health problems of their members. Thus, the FHS model integrates biomedical-institutionalized knowledge with the voice of the community [24]. More recently, nutritionists were incorporated in the FHS and guidelines for diabetes and hypertension have been developed [11], but there are no established guidelines for childhood obesity. Thus, this project will inform possible strategies to be disseminated in the health care system in Brazil.

The results of this study will be submitted for publication in next year and the methods presented may contribute to develop effective interventions to reduce the growing prevalence of obesity. If positive results of the CHA intervention are observed, all CHA from Duque de Caxias, Rio de Janeiro will be trained and materials developed used in the primary health care.

